#### Asthma Self-Monitoring and Personalized Treatment Plans

Incorporating the *self-management* component of the CCM, PEAKmAAP and PEAKmAAP-DS participants will be prompted to complete an asthma symptom checklist or enter a PF rate daily. They will also access PEAKmAAP to enter symptoms or the PF during worsening symptoms, which is an overt cue to action as part of the HBM. Adolescents may be recommended by their asthma care provider or have a personal preference to record either symptoms or the PF. The app is programmed to navigate to the appropriate personalized asthma zone when *either* symptoms or the PF are entered; participants *are not* required to enter both. Once data are entered (PF or symptoms), PEAKmAAP will automatically navigate to a new color-coded green, yellow, or red landing page to provide real-time instructions that correspond to the participant’s personalized green, yellow, or red zone of their AAP. The instructions assist the adolescent in determining when to take controller medications, what the rescue medication dose and frequency are, and when to contact medical personnel according to instructions prescribed by their asthma care provider.

Personalized treatment zones will alert the adolescent to a more accurate level of perceived severity based on their entered data. This will also incorporate the *decision support* component of the CCM. In addition to prompting appropriate action, providing personalized information will address the perceived barrier of not knowing their treatment options by eliminating guesswork, a process that builds self-efficacy, which is key to behavior change. If participants navigate to the green zone, instructions for daily controller medications will appear. If they navigate to the yellow or red zone, instructions for rescue medication dosing and frequency will appear (cue to action), in addition to instructions to take daily controller medications. The PEAKmAAP app will provide several opportunities for *corrective actions* to be taken in the event of acute symptoms:

Follow-up messages will prompt the adolescent to reassess asthma 20 minutes after any yellow or red zone recording. If the adolescent fails to respond, a second prompt will be sent 20 minutes later.If the adolescent enters severe symptoms (eg, lips turning blue, tightness in the throat), the app will automatically navigate to a shortcut prompting them to “Call 911/EMS” or seek emergency care.

In alignment with asthma guidelines [2] and instructions provided on paper-based AAPs, the PEAKmAAP app’s design includes additional cues to action by defining parameters for prolonged or severe exacerbations. A prolonged exacerbation is defined as recording of yellow zone readings on 2 or more consecutive days *or* failing to indicate an improvement (eg, answers no or does not respond to the question, Are you feeling better?) within 48 hours of a yellow zone alert. A severe exacerbation is defined as ≥2 consecutive red zone readings in a ≤1-hour period *or* failing to indicate improvement within 1 hour of a red zone alert. In the event of a prolonged or severe exacerbation, the adolescent will be prompted via PEAKmAAP to contact their doctor. For prolonged or severe exacerbations, an alert will be sent to the participant and study team web portals.

PEAKmAAP is not intended or designed to replace participants’ medical care. Participants will be counseled during the informed consent/assent process regarding the importance of seeking appropriate medical care. Caregivers and participants will be advised to seek appropriate medical care, including the participants’ asthma care providers, emergency care, or the ACH Afterhours Nurse Line for worsening or uncontrolled symptoms. As a safety precaution, trained study personnel will monitor the study team’s web portal during regular business hours and contact the participant’s caregiver within 1 business day of any prolonged or severe exacerbation alert to ensure that appropriate medical attention is sought.

#### Customizable Medication Reminders

Incorporating the *clinical information system* component of the CCM, PEAKmAAP and PEAKmAAP-DS participants will receive daily messages (cue to action) to take controller medication doses. Via push notifications, participants will receive a prompt—“Don’t forget to take your ___ (participant’s controller)!”—once or twice daily as per their personalized AAPs. Monthly prescription refill reminders (cue to action) will be sent via push notifications for all controller medications. The delivery time of the messages and reminders will be customized based on the participants’ preferences (eg, before school on school days, midmorning on weekends, etc).

#### Mobile Educational Tips and Resources

The PEAKmAAP app incorporates multiple media types (as recommended by the CAB), including videos (Table 2), text, and pictures to deliver education. Asthma education tips will be delivered via push notifications (to address perceived severity and perceived susceptibility of asthma exacerbation). Weekly text messages will deliver short tips to reinforce asthma concepts, such as medication adherence, inhaler/spacer technique, knowing the difference between rescue and controller medications, and recognizing asthma symptoms. In addition to receiving these educational tools via push notifications, participants will have access to all educational content through an “Asthma Tips” shortcut on PEAKmAAP’s home screen.

#### National Weather Service Data

Participants will have access to real-time location-specific weather data from the PEAKmAAP home screen [37]. Weather details (weekly forecast predictions of temperatures in Fahrenheit, precipitation, humidity, pollen count, and ozone level) will be provided to help adolescents be more aware of environmental changes that could trigger asthma symptoms.

#### Data Sharing

Data generated by PEAKmAAP and mobile surveys (detailed later) will be shared with the asthma care providers of PEAKmAAP-DS participants monthly. The monthly report will include (1) results of monthly mobile surveys documenting rescue medication use, acute health care visits, and prednisone bursts and (2) PEAKmAAP-generated data regarding prolonged or severe exacerbations (described earlier).

### Summary of Study Visits

#### Screening

Potentially eligible participants were recruited from primary care and specialty clinics at the ACH through direct patient contact and advertising. In addition to direct patient contact in clinics, the research team has received IRB approval to identify potentially eligible subjects through the EHR by prescreening for age and asthma diagnosis eligibility criteria prior to clinic appointments at primary care and specialty clinics. Potentially eligible participants were called prior to their clinic visit to allow research personnel to introduce the study and to ask permission to discuss the study in detail at their upcoming clinic visit. Because ACH patients receive care in other settings, such as the ED and other outpatient clinics, or may be registered in institutional research participant registries, participants were also recruited from these locations.

#### Baseline Visit

Research personnel obtained informed consent and assent from caregivers and adolescent participants, respectively, prior to any study procedures. At the initial visit, baseline data collection included lung function testing, frequency of asthma symptoms, activity limitations, health care use, asthma self-efficacy, and assessment of the dose and frequency of asthma rescue and controller medication. After these baseline data were obtained, participants were randomized to 1 of the 3 arms of the study. After randomization, PEAKmAAP and PEAKmAAP-DS participants received detailed instructions for use of the PEAKmAAP app, including an instructional video to explain all the features of the app, while the eUC participants received detailed instructions for the use of Nutrimap (Table 4).

**Table 4 table4:** Summary of study visit, outcome measures, and survey documents.

Measure	Screening prerandomization	Baseline prerandomization	3 months	6 months	9 months	12 months
Eligibility	X^a^	—^b^	—	—	—	—
ACT^c^ survey	X	Screening ACT score	X^d^	X	X	X^e^
Asthma severity classification	—	X	—	—	—	—
CASI^f^ score	—	X	X	—	—	X^e^
Lung function test with fraction of FeNO^g^	—	X	X^e^	—	—	X^e^
Child Self-Efficacy Survey	—	X	X^e^	—	—	X^e^
Asthma control classification (derived from the ACT survey)	—	X	X^e^	X	X	X^e^
Medication adherence (prescription profile for prior 12 months)	—	X^h^	—	—	—	X^h^
System Usability Scale (SUS)	—	—	—	—	—	X
Medication use (monthly self-report)	—	X	Monthly	Monthly	Monthly	Monthly
Health care use (monthly self-report)	—	X	Monthly	Monthly	Monthly	Monthly

^a^X: applicable.

^b^Not applicable.

^c^ACT: Asthma Control Test.

^d^Primary outcome.

^e^Outcome obtained by blinded research personnel at an in-person visit (all others via a mobile survey).

^f^CASI: Composite Asthma Severity Index.

^g^FeNO: fractional exhaled nitric oxide.

^h^Profile requested directly from insurer, pharmacy data, or medical record.

#### Monthly Surveys

All participants receive a link to a survey each month via push notifications from their mobile app (PEAKmAAP or Nutrimap). The monthly survey asks participants to self-report rescue medication use in the past 2 weeks due to wheezing, coughing, or trouble breathing. The survey also asks participants to record exacerbations resulting in hospitalization, ED or sick visits, or prednisone use in the previous 4 weeks. These data, along with app-generated data on the frequency of green, yellow, and red zone days, will be used to generate the PCP report for PEAKmAAP-DS participants.

#### Three- and Twelve-Month Visits

Three and twelve months after enrollment, an in-person visit will be conducted with all participants to obtain lung function testing results. Blinded research personnel will survey the participants to complete the ACT and self-efficacy questionnaire and to obtain a detailed history on asthma symptoms and activity limitations. The 3-month ACT score is the primary outcome of the study.

#### Six- and Nine-Month Visits

Six and nine months after enrollment, a telephone visit will be conducted to administer the ACT. Research personnel conducting the visit will be blinded to every participant’s treatment arm.

### Summary of Outcome Measures

#### Primary Outcome Measure

The primary outcome measure will be the change in the ACT score of ≤19 (uncontrolled asthma) to >19 (controlled asthma) at 3 months. The ACT is a validated 5-question survey used to assess asthma control in individuals ≥12 years of age. The ACT is used for symptoms monitoring as per guidelines [2], and the ACT score has been identified as an appropriate asthma control composite score in clinical research [26]. The ACT is an efficient, reliable, and validated method of measuring asthma control, with an internal consistency reliability of 0.84 [27]. Mobile and web-based versions of the ACT have been validated [38,39], and we have successfully used the ACT in our pilot studies [21,40].

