**Objective:**

This full-scale RCT will examine the effectiveness of the Pulmonary Education and Asthma Knowledge Mobile Asthma Action Plan (PEAKmAAP), an interactive mHealth asthma action plan (mAAP) smartphone app, among adolescents compared to enhanced usual care (eUC). The study has 3 aims: (1) examine the effectiveness of PEAKmAAP in reducing asthma morbidity, as measured by the Asthma Control Test (ACT) score, health care use, medication use, and lung function; (2) examine the effectiveness of PEAKmAAP in asthma self-efficacy and medication adherence; and (3) examine the impact of sharing PEAKmAAP-generated data with the primary care provider (PCP) for a subset of enrolled subjects. We hypothesize that the PEAKmAAP groups will experience reduced asthma morbidity compared to the eUC group. Furthermore, we hypothesize that PCP data sharing is expected to enhance PCP prescribing patterns and that more adolescents in the Pulmonary Education and Asthma Knowledge Mobile Asthma Action Plan with data sharing (PEAKmAAP-DS) group will have sustained controlled at follow-up visits compared to PEAKmAAP alone or eUC.

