#### Secondary Outcome Measures

##### ACT Survey to Assess Secondary Outcomes

Recognizing that ACT scores may improve but remain ≤19 for some participants with poorly controlled asthma, we will also assess for change in the ACT score that is considered clinically important (as indicated by a ≥3-point increase) [23]. The ACT score will be assessed via a mobile survey to measure for sustained improvement throughout the study. We hypothesize that PCP data sharing will facilitate asthma control by alerting the PCP when asthma worsens or fails to improve. The impact of PCP data sharing on the ACT score will be measured to assess whether data sharing has added any benefit to the PEAKmAAP group.

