Using these models, the primary outcome of the proportion of participants with ACT scores of >19 at 3 months will be analyzed using linear models with a logit link function and contrasts to compare the 2 PEAKmAAP groups combined with the eUC group. Secondary analyses of the proportion of ACT scores of >19 at additional timepoints (6, 9, 12 months) will be assessed with contrasts for the group effect (to measure the average effect across the different timepoints) and the group-by-time interaction effect (to measure the change in effect over time) between groups (PEAKmAAP-DS vs PEAKmAAP; PEAKmAAP groups combined vs eUC). Since the ACT score will be measured at 3, 6, 9, and 12 months (all participants will have baseline scores of ≤19), these correlated repeated measures data will be analyzed with a binomial distribution and a logit link function for modeling with an appropriate correlation structure (eg, compound symmetry or first-order autoregressive). Additionally, minimally important improvements in ACT scores (3-point increase) and CASI (1-point decrease) will be similarly modeled as binary outcomes across timepoints, contrasting eUC versus the 2 PEAKmAAP groups combined or PEAKmAAP versus PEAKmAAP-DS. Other secondary outcomes (health care use, rescue medication use, lung function) will be analyzed using similar models for nonnormal data using appropriate distributions and link functions.

Medication adherence rates at 12 months will be compared using a logistic regression model after adjusting for baseline values as a covariate, contrasting eUC against the 2 PEAKmAAP groups. Mean asthma self-efficacy scores at 3 and 12 months, including the subscales for prevention and management, will be compared among the 3 groups using the analysis of covariance model after adjusting for baseline values as a covariate in the model. The proportion of adolescents who receive step-up therapy will be compared between the 2 PEAKmAAP groups, and the 2 PEAKmAAP groups together will be compared with the eUC across different timepoints using a similar logistic model.

No interim analyses are planned, and thus, there is no planned stopping rule for the study.

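### All ACT and CASI models named in the article are binary; a baseline-adjusted analysis of the scores should be added as supportive secondary evidence, with the primary outcome left as it is

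*Protocol article*

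**What the plan says.** Three places in the protocol article present the ACT score as the outcome. The Objective in the Abstract sets Aim 1 as "reducing asthma morbidity, as measured by the Asthma Control Test (ACT) score", among other measures. The section on the three- and twelve-month visits states: "The 3-month ACT score is the primary outcome of the study". The section on secondary use of the ACT says: "The impact of PCP data sharing on the ACT score will be measured to assess whether data sharing has added any benefit".

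The definitions and models are binary. The Primary Outcome Measure section reads: "The primary outcome measure will be the change in the ACT score of ≤19 (uncontrolled asthma) to >19 (controlled asthma) at 3 months". In Statistical Analysis:

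- the 3-month proportion above 19 "will be analyzed using linear models with a logit link function and contrasts to compare the 2 PEAKmAAP groups combined with the eUC group";
- for ACT control at 3, 6, 9 and 12 months, "these correlated repeated measures data will be analyzed with a binomial distribution and a logit link function";
- "minimally important improvements in ACT scores (3-point increase) and CASI (1-point decrease) will be similarly modeled as binary outcomes", for the combined groups versus eUC and for PEAKmAAP versus PEAKmAAP-DS.

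The sentence on other secondary outcomes lists health care use, rescue medication use and lung function, so it does not bring in the ACT or CASI score. The self-efficacy score, by contrast, is compared as a mean by analysis of covariance. Table 4 shows ACT collected at screening (serving as baseline) and at 3, 6, 9 and 12 months, and CASI at baseline, 3 and 12 months.

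**The concern.** A score cut into two classes loses information. An adolescent who moves from 17 to 19 counts the same as one who does not change, on both ACT criteria. If the app shifts scores modestly in many participants, the binary analyses may miss an effect that the collected scores would show.

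Two things are at stake. First, a borderline responder result on the primary outcome would have no score analysis beside it to show whether the whole distribution moved. Second, the comparison of PEAKmAAP-DS with PEAKmAAP (Aim 3) has one arm on each side, and the Sample Size section gives no power for it. It rests on the less sensitive form of each measure, so an uninformative null is a real risk. CASI is affected too: its own section justifies it as discriminating treatment response better than a symptom-based measure, and a 1-point cut discards part of that advantage.

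**Working it through.** **Inputs from the document.** 107 per group, so 107 eUC versus 214 combined; difference 15%, read as percentage points; two-sided 5%; at least 80% power.

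**Inputs assumed, because the article gives none.** Reference-arm responder rate p of 20-40%; follow-up SD of the ACT score 4; correlation with baseline 0.3-0.5.

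**1. The plan's own figure.** For two proportions with allocation ratio k = 2:

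n = [1.96·√((1+1/k)·p̄(1−p̄)) + 0.842·√(p₁(1−p₁) + p₂(1−p₂)/k)]² / 0.15²

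At p₁ = 0.20, p₂ = 0.35, p̄ = 0.30: [1.96·√0.315 + 0.842·√0.27375]² / 0.0225 = 1.540² / 0.0225 ≈ 105.5, so 106. That agrees with 107 to within one participant, and 107 gives 80.6%. It is not proof of how 107 was obtained, since neither the eUC rate nor the GEE correlation is stated.

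**2. The same effect on the score scale.** A uniform normal shift that raises the responder rate from p to p + 0.15 has standardised size d = z(p + 0.15) − z(p). For 107 versus 214, power ≈ Φ(d·√(107·214/321) − 1.96) = Φ(8.446·d − 1.96). Baseline adjustment divides the residual SD into d with factor √(1 − ρ²), that is, d becomes d/√(1 − ρ²).

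At p = 0.20, d = −0.385 − (−0.842) = 0.456, and power = Φ(3.85 − 1.96) = 97%.

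| Assumed eUC rate | d | Mean difference at SD 4 | Binary, unadjusted | Score, unadjusted | ANCOVA, ρ 0.3 to 0.5 | eUC n for 80% (binary / score, unadjusted) |
|---|---|---|---|---|---|---|
| 20% | 0.456 | 1.8 | 80.6% | 97.1% | 98.1-99.4% | 106 / 57 |
| 30% | 0.399 | 1.6 | 74.2% | 92.0% | 94.2-97.3% | 123 / 75 |
| 40% | 0.379 | 1.5 | 72.0% | 89.3% | 91.9-95.9% | 130 / 82 |

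**3. The fair comparator.** The plan allows adjustment for baseline, so ANCOVA should be set against baseline-adjusted logistic regression, not the unadjusted test. This was simulated with ACT rounded and bounded at 5-25.

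| Comparison, uniform shift | Adjusted logistic | ANCOVA |
|---|---|---|
| 107 vs 214 | 76-86% | 92-99% |
| 107 vs 107, single timepoint | 64-78% | 83-98% |

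The article states no expected difference for PEAKmAAP-DS versus PEAKmAAP; the 15 points are carried over for illustration. Repeating the simulation with another assumed baseline distribution moved the ends of these ranges by up to about 3 points.

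**4. A less favourable effect pattern.** If about a quarter of treated participants gain 7 points and the rest nothing, at the same 15-point responder difference, 107 versus 214 gives about 73-85% for adjusted logistic and 84-92% for ANCOVA. Over both comparisons the gap is then about 2 to 18 points.

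**5. Which improvement goes uncounted.** From 10 to 16 is counted by the 3-point criterion. From 18 to 20 is counted by the cut at 19. From 17 to 19 is counted by neither. Only a gain that ends at or below 19 and is also under 3 points is missed.

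**The case against.** The binary endpoint is deliberate. Eligibility is ACT of 19 or less, the hypotheses concern attaining and sustaining control, and the sample size is built on the proportion above 19 with at least 80% power claimed. The authors saw that some scores would improve yet stay at or below 19, and added the 3-point outcome for that reason. All of this stands, and it is why the primary should not change.

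The size of the gain depends on the effect pattern. A uniform shift favours ANCOVA; with a few large responders, the advantage can shrink to a couple of points. This stands too. The single-timepoint figures also do not represent the planned repeated-measures analysis of PEAKmAAP-DS versus PEAKmAAP over four visits.

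A mean difference of 1.5-1.8 points lies below the 3-point threshold for clinical importance. That threshold is used for change in an individual, so it does not decide whether a group mean difference matters, but the difference should be read beside the responder proportions.

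A fuller analysis plan may contain score models. A reader might infer from the article that the ACT score will never be analysed; the document cannot support that. It does assign ACT and CASI a model type in every analysis it describes, and that type is binary, while three other places speak of the score. This is more than detail left out for brevity.

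**Conclusion.** The point holds as an inefficiency in the secondary analyses. Within the article, the outcome described as the ACT score is served only by binary models, and the same is true of CASI. A baseline-adjusted score analysis was more powerful in every scenario examined: by roughly 13 to 20 points under a uniform shift, and by about 2 to 18 points if the effect sits in a minority. These sizes rest on the assumed responder rate, SD, correlation and effect pattern, none of which the article supplies.

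Three stronger readings are not supported:

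- That the primary outcome is wrong or the design invalid. The cut at 19 is a reasoned definition of control, and 107 is reproducible at an assumed eUC rate of 20%.
- That adding a score analysis restores power to the primary test. It does not; the primary test stays as it is, and the gain is in the supporting evidence.
- That all improvement below 20, or all improvement under 3 points, is invisible. Only improvement failing both criteria goes uncounted.

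The addition is well worth making, most of all for the data-sharing comparison.

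**What to change.** Keep ACT above 19 at 3 months as the primary outcome, and reword the sentence in the three- and twelve-month visit section so that it names responder status. Add the mean ACT score as a supportive secondary outcome: ANCOVA at 3 months with baseline ACT and the severity stratum, and a linear mixed model over 3, 6, 9 and 12 months with the same covariates. Use the two contrasts already planned (combined PEAKmAAP groups versus eUC; PEAKmAAP-DS versus PEAKmAAP) and report mean differences with 95% confidence intervals. Do likewise for CASI at 3 and 12 months.

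No new data or visits are needed. The cost is several tests: two contrasts for each of ACT at 3 months, ACT over follow-up, and CASI make at least 3 × 2 = 6. They should either enter the Holm-Bonferroni family or be labelled supportive and left outside it. Data collection ended in May 2024 and full analysis began in December 2024, so an analysis not already in an unseen plan must carry its date of addition and cannot be presented as prespecified before the data were available.
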